### Outcomes

#### Primary Outcome

The primary outcome includes identifying the difference in 3 attentional bias metrics toward familiar or novel food stimuli at different presentation times. Detailed descriptions of these outcome measures are provided in the “Outcome Measures” section below.

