While some previous studies have suggested a role for visual attentional bias toward familiarity and novelty of stimuli [22], there is a paucity of studies using electroencephalography to examine this, particularly in the context of food choice behavior. Electroencephalography is a noninvasive technique used to measure brain activity in response to stimuli by recording event-related potentials (ERPs). So far, only a few studies have explored integrating electroencephalography, eye-tracking, and dot-probe methods to study attentional bias to food-related stimuli [23]. Of note, no previous study has taken stimulus novelty and familiarity into consideration, nor how the results of this integrated approach associate with the self-report food choices. Familiar stimuli evoke trust and perceived quality from previous positive experiences are suggested to influence an individual’s choices [24]. However, novel products require more cognitive effort to evaluate, leading to longer information processing times [25]. Thus, the main objective of this pilot study is to examine differences in attention to novel compared with familiar food stimuli, using 3 different attention indexes, including electroencephalography, eye tracking, and dot-probe. Indeed, it is hypothesized that participants will exhibit shorter reaction times (RTs) and longer total fixation durations (TFDs) for familiar compared to novel food items, indicating a stronger attentional bias toward familiar foods. In addition, familiar food items will elicit greater P300 amplitudes compared with novel food items, suggesting enhanced attentional engagement and processing.

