### Sample Size

An a priori power analysis was conducted using G Power version 3.1.9.7 (Department of Psychology, Heinrich Heine University Düsseldorf) to determine the appropriate sample size needed to achieve sufficient statistical power for our study. The analysis was designed for an *F* test, with an assumed medium effect size of *F*=0.35, a significance level of α=.05, and a desired statistical power of 0.80. Based on these parameters, the calculated sample size required was 40 participants. Specifically, the number of groups (between-subject factor) was set at 2 (500 ms vs 2000 ms), and the number of measurements (within-subject factor) included 8 (2 stimulus types [familiar or novel] across 4 food categories). In addition, the correlation among repeated measures was conservatively set at 0.5. The medium effect size was chosen based on the existing literature on attentional bias studies, which commonly report medium to large effect sizes [23]. Under these specifications, G Power estimated an achieved power of 0.820, exceeding the commonly accepted threshold of 0.80 for adequate power. This indicates that a sample size of 40 participants is sufficient to detect a medium effect size in our primary outcome using repeated measures ANOVA, ensuring the study is powered to identify meaningful changes while balancing feasibility within the constraints of a pilot study.

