#### Eye Tracking

The eye-tracking component of this study will be conducted using the Tobii Nano Pro (Tobii Tech), a screen-based eye tracker known for its high precision in capturing gaze data. The Tobii Nano Pro offers a sampling rate of 60 hertz, which translates to data collection at intervals of 16.67 milliseconds. This high frequency allows for detailed tracking of eye movements and gaze patterns. To ensure accurate gaze data, a standard 9-point calibration procedure will be performed at the beginning of each session. This process involves directing the participant’s gaze to 9 specific points on the screen to map their eye movements accurately. The calibration will be verified for precision before starting the main trials to ensure reliable spatial and temporal tracking. Participants will be seated approximately 60 cm from the Tobii monitor, which has a resolution of 1600 × 1200 pixels. Participants will be instructed to maintain a still head position and focus attentively on the images displayed on the screen. Participants will view pairs of pictures displayed side by side for 500 or 2000 milliseconds each. Each image pair is matched for shape, color, and background to control for these variables. The following eye-tracking parameters will be measured:

TTFF: time elapsed between the appearance of a picture and the user’s initial gaze fixation within an area of interest. In this case, each product will be defined as a separate area of interest.First fixation duration: time participants gaze at their first fixation point.TFD: length of all fixations within a specific area of interest (in seconds). Average TFD will be used for statistical analyses.Fixation count: number of fixations on stimuli.Eye movement data will be analyzed using Tobi software.

Fixations are defined as periods where the gaze remains stable within a 30-pixel radius for at least 100 milliseconds, and these fixations must be initiated at least 100 milliseconds after picture onset to exclude anticipatory eye movements.

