### Statistical Analysis

ERP data will be preprocessed with EEGLAB v14.1.2 toolbox for MATLAB [33], involving noise removal, epoching from stimulus onset to 1000 milliseconds post stimulus, and averaging across epochs to extract ERP components. Potentials reflecting ocular or muscle-related artifacts were removed using logistic infomax independent component analysis [34]. Further artifacts will be removed using the clean_rawdata plugin for EEGLAB.

Regarding dot-probe and electroencephalography attention-related measures (RTs, and N100 and P300 amplitudes, respectively), repeated measures ANOVA will be conducted, including the stimulus type (familiar vs novel across 4 food categories) as a within-subject factor, and group (500 ms vs 2000 ms) as a between-subject factor. Similarly, ANOVA will also be conducted to examine eye-tracking measures (TTFF, FD) between groups (500 ms vs 2000 ms). Post-hoc analyses will be conducted with Bonferroni adjustments for multiple comparisons. In addition, relationships between eye-tracking measures (TTFF, FD) and ERP components (P300 and N100 amplitudes) will be calculated by the Spearman correlation analysis. IBM SPSS Statistics 20 (IBM Corp) software will be used to analyze the data. No interim analyses are scheduled for this study.

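### The primary outcome spans three metrics (five variables) at a single 0.05 level with no rule for combining them, and the eye-tracking variable is named inconsistently

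*Protocol article*

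**What the plan says.** The Introduction sets the main objective as comparing attention to novel and familiar foods "using 3 different attention indexes, including electroencephalography, eye tracking, and dot-probe". It gives directional hypotheses for three variables: RT, TFD and P300.

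The Primary Outcome section reads: "The primary outcome includes identifying the difference in 3 attentional bias metrics toward familiar or novel food stimuli at different presentation times". It refers to Outcome Measures, where Textbox 1 lists five variables: TTFF, TFD, RT, P300 and N100.

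Sample Size treats the primary outcome as one test, with "a significance level of α=.05, and a desired statistical power of 0.80".

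Statistical Analysis has two parts that matter here:

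- **Dot-probe and EEG.** "Regarding dot-probe and electroencephalography attention-related measures (RTs, and N100 and P300 amplitudes, respectively), repeated measures ANOVA will be conducted", with stimulus type as the within-subject factor and presentation time as the between-subject factor.
- **Eye tracking.** "ANOVA will also be conducted to examine eye-tracking measures (TTFF, FD) between groups (500 ms vs 2000 ms"; no stimulus-type factor is named in that sentence.

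The only multiplicity statement is: "Post-hoc analyses will be conducted with Bonferroni adjustments for multiple comparisons".

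On the eye-tracking measure, the Eye Tracking section lists four recorded parameters and adds: "Average TFD will be used for statistical analyses". The analysis section instead names FD, which the abbreviation list expands as fixation duration, in an entry separate from TFD.

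**The concern.** The primary outcome can be met by several routes, and the plan does not say which of them count. It names no lead variable, order of testing, division of alpha or requirement that the metrics agree. The Bonferroni statement concerns post hoc comparisons, so it does not control error across the metrics that together form the primary outcome. The 0.05 in Sample Size is then the error rate of one test. It is not the error rate of a claim that familiar and novel foods differ in attention on at least one metric.

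The naming conflict adds to this. TFD is the only eye-tracking variable with a stated hypothesis, yet the analysis section does not name it, and the comparison written there is not familiar versus novel. A reader of the results could not check from the protocol whether the planned eye-tracking test was the one reported.

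**Working it through.** **1. The plan's own power figure.** Inputs from Sample Size: f = 0.35, alpha = 0.05, 2 groups, m = 8 measurements, correlation 0.5, N = 40. For the between-subject factor:

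- λ = f²·N·m / (1 + (m − 1)ρ) = 0.1225 × 40 × 8 / 4.5 = 8.71, with 1 and 38 degrees of freedom.
- Power = 0.820, which matches the stated value. N = 38 gives 0.799, so 40 is the smallest even N that reaches 0.80.
- The within-subject and interaction calculations on the same inputs give more than 0.999, so they do not match.

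The 0.820 is therefore power for the 500 vs 2000 ms between-group effect, not for familiar versus novel.

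**2. How many tests.** Read literally, stimulus type is a factor only in the ANOVAs of RT, N100 and P300, which gives three familiarity tests. If the eye-tracking ANOVA is meant to have the same structure, TTFF and the fixation-duration measure bring the count to five.

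**3. Chance of at least one false positive**, each test at 0.05, if any one counts:

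- Three independent tests: 1 − 0.95³ = 0.143.
- Five independent tests: 1 − 0.95⁵ = 0.226.

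The document gives no correlation between outcomes. The correlated rows below are assumptions, from simulation of equally correlated two-sided normal tests.

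| Assumed correlation | 3 tests | 5 tests |
|---|---|---|
| 0 (independent) | 14.3% | 22.6% |
| 0.3 | 13.7% | 20.8% |
| 0.5 | 12.5% | 18.3% |
| 0.7 | 11.0% | 14.8% |
| 0.9 | 8.4% | 10.1% |

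Every entry is above 5%.

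**4. Cost of adjusting over three primary tests.** The first Holm step is 0.05 / 3 = 0.0167. Even plain Bonferroni at that level gives 1 − (1 − 0.0167)³ = 4.9% for independent tests. For a two-level familiar/novel within-subject contrast on the plan's inputs:

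- λ = f²·N·m / (1 − ρ) = 0.1225 × 40 × 2 / 0.5 = 19.6, with 1 and 38 degrees of freedom.
- Power is 0.991 at alpha 0.05 and 0.969 at 0.0167.

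Holm's later steps use larger alphas, so 0.969 is the lower bound per metric.

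**5. The eye-tracking variable, place by place.**

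| Place | Variable named |
|---|---|
| Introduction and Principal Findings (hypothesis) | TFD |
| Outcome Measures | TTFF, TFD |
| Eye Tracking | four parameters recorded; average TFD for analysis |
| Statistical Analysis | TTFF, FD; 500 vs 2000 ms only |

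**The case against.** **The inflation is conditional.** The protocol never says that one significant metric suffices, and the Introduction words the RT and TFD hypotheses jointly. If all metrics had to agree, alpha would not be inflated. This stands, and the figures are given on that condition. But the protocol does not state an all-must-agree rule either, and the gap is exactly that neither rule is fixed.

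**It is a pilot, and an analysis plan may exist.** The study seeks preliminary data, and detailed multiplicity rules often sit elsewhere. This lowers the weight of the point but does not remove it. The document states directional hypotheses, claims adequate power for its primary outcome and keeps a separate exploratory tier that does not hold these comparisons. It also fixes alpha and the scope of the adjustment itself, and a later plan would inherit the FD/TFD conflict.

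**FD is probably only a slip for TFD.** That is the likeliest reading, since the outcome list and the Eye Tracking section both name TFD. It still needs correcting, because first fixation duration is recorded as well and FD could be taken for it.

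**Stronger readings that do not hold.**

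- A reader might count all three F effects on all five variables, 15 tests, and quote a far higher error rate. The main effect of presentation time is not a familiarity bias, and the protocol does not state three effects for the eye-tracking measures.
- A reader might treat first fixation duration and fixation count as further routes to a primary claim. They are listed only as recorded parameters and appear in neither the outcome list nor the analysis.
- A reader might price the correction from the plan's 0.820, which drops to 0.672 at 0.0167. Both figures belong to the between-group duration effect, not to the contrast being adjusted.

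**Conclusion.** The point holds in conditional form. As written, the plan does not hold a 5% error rate for a claim based on any one metric. If such a claim is allowed, the rate is 14.3% for the three variables literally tested for familiarity and 22.6% if all five are tested, assuming independence. At assumed correlations of 0.3 to 0.9 it is about 14% to 8% and 21% to 10%. These figures count one familiarity test per variable.

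Separately, and without any assumption, the hypothesised eye-tracking variable and the one named in the analysis do not match, and the eye-tracking ANOVA as described does not test familiar against novel.

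This should be corrected before analysis. It does not invalidate the design, and nothing in the documents shows that selective claiming is intended.

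**What to change.** 1. In Primary Outcome, name RT, TFD and P300 as the primary variables. They are one per modality and already carry the Introduction's hypotheses, so they fit the stated count of three metrics.
2. In Statistical Analysis, test the familiar-versus-novel effect on each of the three with Holm across them, and keep Bonferroni for post hoc comparisons.
3. Make TTFF and N100 secondary.
4. Replace FD with TFD in Statistical Analysis, and include stimulus type as a within-subject factor in the eye-tracking ANOVA.

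Other choices would also control error, such as naming a single primary variable. This one stays closest to what the protocol already hypothesises.

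**Cost.** A few sentences, plus a dated update to the Open Science Framework registration. The Results section says analysis is to start only once data collection is complete, so the choice can be recorded before results are seen if that is still so. Statistically, power for a two-level familiarity contrast falls from about 0.99 to no lower than about 0.97 per metric, if f = 0.35 and a correlation of 0.5 apply to that contrast at N = 40. The plan's 0.820 should not be quoted as the baseline for this loss.

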#### Secondary Outcomes

The secondary outcomes focus on evaluating the correlations between ERP data obtained from electroencephalography recordings and the metrics captured through eye tracking and RTs from the dot-probe task.

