### Study Design

This nonrandomized pilot study aims to use different measures of attention, via an integrated eye tracking and electroencephalography methodology, to study different aspects of the food-related attentional bias. Synchronization will ensure that eye movements and neural responses are recorded concurrently in response to the same stimuli during the dot-probe task, allowing precise alignment of data for accurate analysis.

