
#### Software Coordination

The E-Prime software will be integral for stimulus presentation and task control. It will manage the timing of stimulus presentation and coordinate trigger signals to synchronize the eye-tracking and electroencephalography systems. E-Prime will insert data markers into both the eye-tracking and ERP data streams at the beginning and end of each stimulus presentation, ensuring precise alignment of the data during analysis. For temporal accuracy, eye-tracking data will be aligned with ERP data using timestamps from the synchronization triggers, ensuring that each data point from the eye-tracker corresponds to the same point in time as the neural data. Any potential latency differences between the systems will be identified and corrected during the data analysis phase using these synchronized timestamps. A custom script in MATLAB will integrate the eye-tracking and ERP data based on synchronization markers provided by E-Prime.

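### No stated analysis uses the trial-level gaze–EEG alignment: the planned Spearman correlation of averaged measures can show an association between people, but on its own not coupling within people

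*Protocol article*

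**What the plan says.** Study Design has gaze and EEG recorded concurrently on the same stimuli, "allowing precise alignment of data for accurate analysis". Software Coordination adds event markers in both data streams, correction of latency differences, and this step: "A custom script in MATLAB will integrate the eye-tracking and ERP data based on synchronization markers".

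The data are then reduced. Statistical Analysis describes "averaging across epochs to extract ERP components". Eye Tracking states: "Average TFD will be used for statistical analyses". Statistical Analysis relates time to first fixation and fixation duration to P300 and N100 amplitude by Spearman correlation. It gives no unit of analysis, no repeated-measures or multilevel term, and no role for presentation time in that correlation.

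Secondary Outcomes defines the target as "evaluating the correlations between ERP data obtained from electroencephalography recordings and the metrics captured through eye tracking and RTs". Reaction time is therefore part of the secondary outcome, but the Spearman sentence does not include it. In the Discussion, Principal Findings expects the correlation to show that neural and ocular markers contribute jointly to attentional bias, and describes the integration as capturing the neural dynamics beneath attention.

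**The concern.** A correlation of participant means asks whether people who look longer on average also have larger ERPs on average. Trial-level alignment makes a different question answerable: whether, in the same person, gaze and neural response move together from one display to the next. The Discussion leans towards that second, process-level reading, while the stated test addresses the first.

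Two things are at stake. Real within-person coupling could be missed almost entirely, or a correlation driven by stable differences between people could be described as joint processing. Separately, presentation time is treated as a between-subject factor and bounds how long anyone can fixate. A pooled correlation can then arise because the two groups differ on both measures.

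**Working it through.** **1. The plan's own power figure.** Sample Size gives "a significance level of α=.05, and a desired statistical power of 0.80", "with an assumed medium effect size of *F*=0.35", 2 groups, 8 measurements, correlation 0.5 and N = 40. For the between-group test, λ = f²·N·m / (1 + (m−1)ρ) = 0.1225 × 40 × 8 / 4.5 = 8.71 with 1 and 38 df. Power is 0.8202, which matches the stated 0.820. The within-factor and interaction tests give about 1.00 and do not match. The figure therefore covers a 500 ms versus 2000 ms comparison and says nothing about the correlations.

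**2. Detectable correlation.** For 80% power at two-sided 0.05, Fisher z gives tanh(2.802/√37) = 0.43 for n = 40 and tanh(2.802/√17) = 0.59 for n = 20. The n = 20 case is one presentation group; an equal split is assumed. With the Spearman variance factor 1.06 these become 0.44 and 0.60.

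**3. What averaging leaves of within-person coupling.** Let s be the share of variance lying between people, r_b the between-person correlation, r_w the within-person trial correlation, and T = 128 trials (Dot-Probe Task). The correlation of person means is

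(r_b·s + r_w·(1−s)/T) / (s + (1−s)/T).

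The documents do not give s, r_b or r_w; all are assumed. With r_b = 0, r_w = 0.3 and s = 0.3, this is 0.3 × 0.00547 / 0.30547 = 0.005. For s = 0.1 it is 0.020 and for s = 0.5 it is 0.002. All are far below the detectable 0.44.

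**4. Simulation** (40 people × 128 trials, 2000 runs, s = 0.1 to 0.5). The trial-level test is a per-person Spearman correlation, Fisher-transformed, with a one-sample t test over people. It stands in for a mixed model. Entries are the proportion of runs significant at 0.05.

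| Truth | Person means | Trial level |
|---|---|---|
| No correlation at either level | 0.04–0.05 | 0.04–0.05 |
| r_w = 0.1 or 0.3, r_b = 0 | 0.04–0.06 | about 1.00 |
| r_b = 0.5, r_w = 0 | 0.83–0.88 | 0.05–0.06 |
| r_b = 0.5, r_w = −0.3 | 0.80–0.88 | about 1.00 |

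In the last row the person means correlate positively although the coupling is negative. For s = 0.3, (0.15 − 0.00164) / 0.30547 = 0.49.

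**5. Weaker coupling and lost trials.** For r_w = 0.05, approximate trial-level power is Φ(0.05 × √(40 × 125) − 1.96) = Φ(1.58) = 0.94. A simulation with shares 0.3 (gaze) and 0.2 (ERP) gave the same 94%, against about 5% for person means. If only 64 trials per person survive, it is Φ(0.05 × √(40 × 61) − 1.96) = Φ(0.51), about 0.70.

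**6. Other units that fit the wording.**
- Pooling 320 person-by-cell means (40 × 8) as independent points rejects in 0.31–0.48 of runs when there is no correlation at either level.
- Familiar-minus-novel differences, one per person, reject in 0.05–0.06 when only stable level differences are correlated, and have power 0.42–0.44 at r_w = 0.3. This assumes people do not differ in their true bias.

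**7. Pooling the presentation groups.** Fixations must start at least 100 ms after picture onset. If the gaze window ends with the display, fixation time is at most 400 ms in one group and 1900 ms in the other. Assume 20 per group, no correlation within either group, and shifts of 2 SD in gaze and 0.5 SD in ERP. The pooled correlation is then 0.25 × 2 × 0.5 / √[(1 + 0.25 × 4)(1 + 0.25 × 0.25)] = 0.25/1.458 = 0.17, and the test rejects in 19% of simulated studies. With a 2 SD gaze shift, rejection is 5%, 10% and 40% for ERP shifts of 0, 0.3 and 0.8 SD. For scale, the group effect behind step 1 is 2 × √(8.71/40) = 0.93 SD of the person mean, so ERP shifts of this order are within what the plan itself set out to detect.

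**The case against.** The strongest reply is that the plan sets no within-person target. Objectives asks for preliminary data on potential correlations. The Introduction and Discussion motivate the combination of methods by the poor reliability of single tools, so agreement between tools across people is a coherent pilot question. For that null the person-mean test is correct, with 4–5% rejections in step 4. This stands. A reader might infer that the planned correlation is invalid, or that a significant result driven by stable person differences would be a false positive. The documents support neither: such a result is a true association between people, and would mislead only if reported as coupling.

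A reader might also infer that the plan commits to correlating 40 participant means. It does not say so. Its ANOVA needs averages by stimulus type and category, and difference scores also fit the wording. With difference scores, stable level differences no longer produce a result and some power for coupling remains (step 6). This too stands, and limits the blindness claim to the participant-mean reading.

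Nor is the alignment idle: event markers time-lock epochs and gaze windows and correct latency. What is missing is narrower, namely any stated analysis of paired trial values.

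Finally, the simulated contrasts follow from assumed correlations, and the article already concedes reduced power for smaller effects. Both are fair. The near-blindness itself does not depend on the exact values, as the formula in step 3 shows.

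A condensed article may leave the level of a correlation to a fuller plan. This one, however, does name the averaging and the test, and attaches a process-level interpretation to the result.

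**Conclusion.** The concern holds in limited form. The plan collects aligned trial data, and its stated analysis does not use them as pairs. On the participant-mean reading, the Spearman correlation is a sound between-person measure that can detect correlations of about 0.43–0.44 or larger with all 40 participants, or 0.59–0.60 within one presentation group of 20. It has essentially no power for coupling within people (4–6% in the settings tried) and alone cannot support the process-level statements in the Discussion. Pooling the two presentation times can add spurious correlation, from 5% to 40% rejections for ERP shifts of 0 to 0.8 SD with a 2 SD gaze shift.

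These sizes rest on assumed variance shares, correlations and group shifts, an equal split, and all 128 trials being usable. The conclusion does not extend to replacing the Spearman analysis, nor to calling it wrong for the question it answers. The matter should be settled before analysis, which the article says has not begun.

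**What to change.** 1. State the unit of the Spearman correlations. If it is the participant mean, keep them, label them as between-person, and adjust for or stratify by presentation time. Person-by-cell means should not be pooled as independent points.
2. Add a trial-level mixed model for single-trial P300 amplitude, one for N100 amplitude and one for reaction time; the last covers the part of the secondary outcome that the Spearman sentence omits. The predictor is one defined gaze measure per trial, for example familiar-minus-novel fixation time, since each display shows two foods and each is its own area of interest. Centre it within participant, and include the participant mean, presentation time, and a random intercept and slope per participant.
3. Define before analysis how trials without a qualifying fixation are handled. Also define a single ERP epoch onset: Electroencephalography Acquisition starts the epoch at the dot, Statistical Analysis at stimulus onset.
4. Limit statements about joint gaze–neural processing to the trial-level model.

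**Cost.** No new data are needed. The planned MATLAB integration supplies the alignment, but single-trial amplitudes must still be extracted and three models fitted. Single-trial amplitudes are noisy, and trials will be lost to artifacts and missing fixations, especially at 500 ms. The gain in power depends on correlations that are not known in advance.
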